### 2.13 Patient and public involvement

Patients and the public will not be involved in the design, recruitment, conduct, or reporting of this study. The study results will be communicated to participants through email.

### 2.14 Principles and methods of unblinding or breaking the blind

#### 2.14.1 Unblinding timeline

Participants will be unblinded after the study concludes, once all subjects have completed the 1-month follow-up period. Unblinding Method: An independent DMC will manage the unblinding process, overseeing and securely retaining all randomization data until the scheduled unblinding.

#### 2.14.2 Emergency unblinding

In the event of a serious adverse event (SAE) or other emergency during the trial, unblinding will be conducted immediately to ensure appropriate medical intervention. The principal investigator will request emergency unblinding from the DMC, with the reasons and process for unblinding fully documented.

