### 2.7 Randomization and blinding

An independent researcher will generate random numbers using an online tool (https://www.sealedenvelope.com/simple-randomiser/v1/lists) with a 1:1:1 allocation ratio. The randomization results will be stored in sealed, opaque envelopes. Patients will be assigned to the fentanyl, nalbuphine, or placebo group. A nurse anesthesiologist not involved in other study procedures will prepare fentanyl, nalbuphine, and saline in syringes labeled only with patient numbers, which will also be marked on the outer packaging. Patients, surgeons, anesthesia providers, outcome assessors, and statisticians will all be blinded to group assignments.

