### 2.10 Data collection and monitoring

Data collection will include baseline characteristics such as age, sex, BMI, comorbidities, smoking status, alcohol consumption, education level, and scores from the Hospital Anxiety and Depression Scale (HADS), as well as the number of painless examinations. All data will be documented in case report forms (CRFs) and subsequently entered into the electronic database under the supervision of the principal investigator. An independent Data Monitoring Committee (DMC) will continuously monitor the data collection process. Once data registration is complete, the electronic database will be secured. De-identified datasets will be provided to an independent statistician for analysis based on a predefined plan. Serious adverse events (SAEs), related or unrelated to the study medication (e.g., persistent severe psychiatric symptoms), must be promptly reported to the principal investigator. The perioperative care team will take necessary actions to ensure participant safety, and these events must be reported to the DMC within 24 h for further evaluation and possible adjustments or study termination. To ensure the integrity and accuracy of the collected data, we implemented the following measures: A double-check mechanism for data entry, where all data entries are verified by a second independent researcher; Regular audits of the collected data to identify and correct any inconsistencies or errors; Standardized training for all researchers involved in data collection to ensure consistent protocols and reduce the risk of errors.

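### The emergency rule in section 2.14.2 breaks the blind for any SAE without asking whether the allocation is needed for the patient's care

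*Protocol article*

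**What the plan says.** Section 2.14.2 of the protocol article sets the trigger: "In the event of a serious adverse event (SAE) or other emergency during the trial, unblinding will be conducted immediately". The same sentence gives the aim: "unblinding will be conducted immediately to ensure appropriate medical intervention". The route follows: "The principal investigator will request emergency unblinding from the DMC", "with the reasons and process for unblinding fully documented".

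Section 2.10 defines which SAEs must be reported to the principal investigator: "Serious adverse events (SAEs), related or unrelated to the study medication". Its one example is lasting severe psychiatric symptoms, which could appear during follow-up. On onward reporting it says: "these events must be reported to the DMC within 24 h for further evaluation".

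Section 2.7 keeps patients, surgeons and anesthesia providers blinded, and adds: "outcome assessors, and statisticians will all be blinded to group assignments". Section 2.14.1 keeps participants blinded until everyone has finished the 1-month follow-up and has the DMC retain the randomization data until then. Sections 2.7 and 2.8 also place the assignments in sealed opaque envelopes, without naming the holder.

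**The concern.** The usual test for breaking one patient's code is whether knowing the arm would change how that patient is treated. Section 2.14.2 uses a different test, the occurrence of an SAE or other emergency, and says that unblinding will then take place. An SAE is defined by seriousness, not by any link to the study drug, so the two tests can part company. Here the study opioid or saline is given once, at induction, while follow-up runs to 1 month. An unrelated hospital admission in week 3 would meet the trigger although the allocation may have no bearing on care.

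What is at stake is the credibility of the later scores. The Discussion accepts that the euphoria measures are self-reported and open to response bias. A patient who learns that the drug was fentanyl, nalbuphine or saline could answer the next euphoria questionnaire differently. If SAEs were more frequent in one arm, the loss of blinding would also be unequal between arms.

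**Working it through.** The plan gives no figure on this point, so there is none to reproduce. The check is a comparison of sections, followed by a bound on size.

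**Step 1: is there a test of need?** Section 2.14.2 has a trigger (SAE or other emergency), an instruction (unblinding will be done at once), a purpose (appropriate treatment), a route (principal investigator to DMC) and a record (reasons and process). The purpose explains why the rule exists. The record describes what is written down when it is used. Neither says that the code stays closed when the allocation is irrelevant to care.

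**Step 2: which events meet the trigger?** Section 2.14.2 does not define an SAE. The scope in section 2.10 includes unrelated events. Read together, an unrelated SAE meets the literal trigger.

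**Step 3: what happens to the data?** Section 2.12 keeps every participant with relevant data in the mITT set, whatever their adherence, and enters MBG scores at 30 min, 1 week and 1 month in one mixed model. A code break made under section 2.14.2 follows the protocol, so it is not clear that the per-protocol analysis would exclude the patient either.

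**Step 4: how many patients?** Inputs: N = 285 (section 2.1); SAE proportion p is not in the documents and is assumed to lie between 0.1% and 3%. Patients unblinded = N × p.

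| Assumed p | Calculation | Patients |
|---|---|---|
| 0.1% | 285 × 0.001 | 0.285, about 0.3 |
| 1% | 285 × 0.01 | 2.85, about 3 |
| 3% | 285 × 0.03 | 8.55, about 9 |

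**Step 5: how many scores?** If the break comes after the 30-min interview, at most 2 of a patient's 3 MBG scores follow it. With complete data the model holds 285 × 3 = 855 scores.

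- At p = 0.1%: 0.285 × 2 = 0.57 scores, and 0.57 / 855 = 0.07%.
- At p = 3%: 8.55 × 2 = 17.1 scores, and 17.1 / 855 = 2.0%.

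These are upper limits for each assumed p: a break in week 3 exposes only the 1-month score, and exposure requires that the patient or the assessor actually learns the arm.

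**The case against.** The strongest reply is that section 2.14.2 is a two-sentence rule in a condensed article and is being read harshly. Its heading limits it to emergencies, it names treatment as the aim, and it has the principal investigator make a request with reasons; an automatic break would need neither request nor reasons. The phrase on related and unrelated events belongs to the reporting rule in section 2.10, where the consequence is DMC evaluation, not unblinding.

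Part of this stands. The investigators may well intend case-by-case judgement, and the combination of the two sections is an inference. However, the text says that unblinding will be done, and nothing in it lets the principal investigator decline to ask. Since the rule is stated rather than left out, condensation does not excuse it.

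Three stronger readings are tempting, and the documents do not support them:

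- **That the DMC route delays an urgent code break.** The 24 h in section 2.10 is an outer limit for safety reporting, not the time to release a code. The DMC may be reachable at any hour, and the full protocol may say so.
- **That outcome assessors or data staff will learn the allocation.** The principal investigator makes the request and data are "entered into the electronic database under the supervision of the principal investigator", but supervising entry is not assessing outcomes, and section 2.10 has a second independent researcher verify entries. Nothing in section 2.14.2 lifts the blinding in section 2.7 for assessors or statisticians.
- **That the primary outcome is at material risk.** An SAE during the procedure could lead to a break before the 30-min interview. Bias would also require that the patient or assessor be told and that the interview still take place on time. The documents establish neither.

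**Conclusion.** The point holds as a flaw in the wording of a stated rule. On its literal terms, section 2.14.2 breaks the blind for SAEs where the allocation does not matter to care, and the self-reported scores of those patients remain in the main analysis. This rests on reading the trigger with the SAE scope in section 2.10, and on the absence of any stated test of need.

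The consequence is probably small. The patient counts depend wholly on the assumed SAE range, for which the documents offer no support in either direction. Exposure falls mainly on the 1-week and 1-month scores, which are secondary, rather than on the 30-min MBG score. Sample size, alpha and power are unaffected. It is a cheap improvement and not a threat to the trial's main conclusion.

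**What to change.** Reword section 2.14.2 so that:

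- the code is broken for a single participant, and only when knowing the allocation is needed for that participant's care;
- the allocation is disclosed only to those who need it for that care;
- outcome assessors, data-entry staff and the statistician stay blinded;
- the time of the break is logged with the reason;
- the participant is flagged, and a sensitivity analysis leaves out scores collected after the break.

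Custody can stay with the DMC; moving it to the site would be a separate governance choice that this point does not require. Sections 2.7, 2.8, 2.10, 2.14.1 and 2.14.2 should be reconciled to say who holds the code, what role the sealed envelopes have, and who can release an allocation at once.

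The cost is a paragraph of wording, some extra logging, and one additional analysis, which will be trivial if few or no codes are broken.

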## 3 Discussion

This study is a single-center, randomized, double-blind, placebo-controlled trial involving 285 adult patients scheduled to undergo bidirectional gastrointestinal endoscopy. The primary objective is to evaluate the differential effects of intravenous propofol administration combined with fentanyl, nalbuphine, or normal saline on patient-reported euphoria during painless endoscopy. The primary outcome measure is the Morphine-Benzedrine Group (MBG) subscale score of the Addiction Research Center Inventory (ARCI), which assesses drug-induced euphoria. ARCI is a validated psychometric instrument developed by the National Institute of Mental Health Addiction Research Center, comprising MBG, PCAG, and LSD subscales that assess drug-induced euphoria, sedation, and anxiety, respectively. Specifically, the MBG subscale quantifies euphoric effects and helps determine whether patients experience significant euphoria. Secondary outcomes, including sedation and anxiety, will also be evaluated systematically at 30 min, 1 week, and 1 month after the procedure through questionnaires and ARCI scores, and related influencing factors will be analyzed statistically. This study will be conducted in accordance with the CONSORT guidelines. The trial will be conducted and reported in accordance with the Consolidated Standards of Reporting Trials (CONSORT) guidelines. To control for potential confounding effects and ensure the validity of the primary results, baseline covariates will be adjusted using appropriate statistical methods. Additionally, sensitivity analyses will be performed to assess the robustness and consistency of the findings.

Propofol is a γ-aminobutyric acid (GABA) receptor agonist that enhances the function of GABA type-A receptors (GABA_AR) on the postsynaptic membrane, thereby exerting sedative, anxiolytic, and antiepileptic effects (Yang et al., 2011). It is currently among the most commonly administered intravenous anesthetics in clinical practice worldwide (Baker and Naguib, 2005; Trapani et al., 2000; Solomon et al., 2019). Due to its rapid onset and short half-life, propofol has become particularly favored for sedation during gastrointestinal endoscopy (Walsh, 2022). However, recent increases in reported cases of propofol addiction have raised significant concern among both healthcare providers and the broader community. Clinical studies have indicated that more than half of patients receiving propofol report subjective sensations of relaxation, pleasure, or euphoria (Kim et al., 2013; Brechmann et al., 2018). Animal studies further support these findings, demonstrating that rats can reliably distinguish propofol from control solvents and exhibit reward-associated behaviors, suggesting propofol’s potential for addiction (Zacny et al., 1993; Shahzadi et al., 2018). Emerging evidence suggests that the mesolimbic-cortical pathway—particularly the neuronal circuitry linking the ventral tegmental area (VTA) to the nucleus accumbens (NAc) and prefrontal cortex—as well as various neurotransmitters and their corresponding receptors, plays a critical role in mediating the euphoric and rewarding effects induced by propofol (Dong et al., 2021; Chen et al., 2020; Yang et al., 2011).

During gastrointestinal endoscopy, sedation with propofol combined with fentanyl is a commonly used clinical regimen (Luginbuhl et al., 2009). Fentanyl, a potent synthetic opioid analgesic approximately 50–100 times more potent than morphine, has recognized addictive potential and induces pronounced euphoria through activation of the μ-opioid receptor (MOR) and associated reward pathways (Vardanyan and Hruby, 2014; Volkow et al., 2019). Given these pharmacological characteristics, fentanyl may modulate patients’ subjective responses to propofol, potentially intensifying its euphoric effects.

Nalbuphine is a mixed opioid agonist-antagonist characterized by its dual pharmacological effects: κ-opioid receptor agonism and μ-opioid receptor antagonism (Errick and Heel, 1983). Compared with traditional opioids such as morphine and fentanyl, nalbuphine primarily achieves analgesia through κ-receptor activation, while its antagonistic effect on μ-receptors significantly reduces associated euphoria, respiratory depression, and risk of dependence (Ibrahim et al., 2018; Hammond, 1984; Jannuzzi, 2016). Due to these pharmacological characteristics, nalbuphine has a notably lower abuse potential and has been increasingly used in endoscopic sedation in recent years (Li S et al., 2021). Considering nalbuphine’s antagonistic action on μ-receptors—key mediators of opioid-induced euphoria—it is plausible to hypothesize that when combined with propofol, nalbuphine might attenuate or counteract propofol-induced euphoric effects, potentially offering clinical benefits in sedation strategies aimed at reducing drug dependence risk.

We note that missing data will not be imputed. The rationale behind this approach is to avoid introducing potential bias by making assumptions about missing values, particularly in the absence of a clear pattern of missingness. Furthermore, since most of our data were collected in a hospital setting, the missing data represent only a very small fraction of the overall dataset. Given that the missing data are unlikely to be systematically related to key variables, we believe that imputation could introduce unnecessary assumptions that may not accurately reflect the true data distribution.

This study has several limitations. First, as a single-center trial, the generalizability of the results to broader clinical settings may be limited; multi-center studies involving diverse patient populations would be necessary to validate these findings. Second, the relatively short follow-up duration (1 month) restricts the evaluation of potential long-term euphoric effects and addiction risks associated with repeated exposure to propofol and opioid combinations. Extended follow-up periods would provide deeper insights into the chronic implications of these sedation regimens. Third, the exclusion criteria—especially excluding patients with long-term opioid or sedative usage—may introduce selection bias, limiting the external validity of the results. Including such patient groups in future research could yield a more comprehensive understanding of drug-related addictive risks. Fourth, the primary outcomes of this study rely on subjective self-reported measures of euphoria, which might be susceptible to response bias; incorporating objective biomarkers or neuroimaging techniques in future studies could enhance the objectivity of the findings. Lastly, the current study design does not include objective behavioral assessments of addiction-related behaviors, such as drug-seeking actions, thereby limiting the evaluation of true addiction potential. Future investigations should explore other sedative drug combinations and their potential effects on euphoria, as well as further examine objective behavioral events related to addiction.

The primary aim of this randomized, double-blind, placebo-controlled trial is to evaluate the differential effects of intravenous propofol combined with fentanyl, nalbuphine, or placebo on patient-reported euphoria following painless gastrointestinal endoscopy. By systematically examining the impact of these sedation regimens, the study seeks to determine whether fentanyl amplifies, or nalbuphine mitigates, propofol-induced euphoric sensations. The findings are anticipated to provide robust clinical evidence to guide sedation strategies, potentially optimizing postoperative sedation protocols and enhancing patient safety and outcomes in gastrointestinal endoscopic practice. Additionally, if the results confirm that nalbuphine reduces euphoria compared to fentanyl, this could lead to safer sedation protocols by minimizing the risk of addiction-related side effects.

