### 2.4 Primary outcome

The primary outcome will be the Addiction Research Center Inventory (ARCI) - Morphine–Benzedrine Group (MBG) scores, assessed via in-person interviews at 30 min post-awakening. The ARCI scale was developed by the National Institute of Mental Health Addiction Research Center (United States). The MBG, a subscale of the ARCI, measures drug-induced euphoria and helps assess whether patients experience euphoria. The MBG consists of items 1 to 16, and the sum of these items represents the euphoria score. The Chinese version used in this study was translated by experts, with its reliability and validity confirmed.

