### 2.5 Secondary outcomes

Secondary outcomes will include ARCI-MBG scores at 1 week and 1 month postoperatively; ARCI total scores at 30 min post-awakening, 1 week, and 1 month postoperatively; ARCI-Pentobarbital, Chlorpromazine, Alcohol Group (PCAG) scores at 30 min post-awakening, 1 week, and 1 month postoperatively; ARCI-Lysergic Acid Diethylamide (LSD) scores at 30 min post-awakening, 1 week, and 1 month postoperatively; Pittsburgh Sleep Quality Index scores at 1 week and 1 month postoperatively; and dream descriptions (none, pleasant, or nightmare) at 30 min post-awakening; The Surgical Pleth Index assessed at the time of endoscope insertion.

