### 2.11 Sample size calculation

Based on the previous study (Li et al., 2024), the mean ARCI-MBG score 30 min after patients wake from gastrointestinal endoscopy is 8.84 with a standard deviation of 2.22. To detect a difference of 0.5 standard deviations between groups, and using the Bonferroni correction with a significance level of 0.017% and 80% power, we calculated a sample size of 95 patients per group. Considering a 10% dropout rate, the total required sample size is 285 patients, assuming a two-sided α of 0.05% and 80% power.

To calculate the sample size, we used the following formula for two independent groups with a normal distribution: n=(Z_1−α′/2_+Z_1−β_)^2^ × 2/d^2^.

Where: Z_1−α′/2_ is the critical value for a two-sided α′ of 0.017 (2.396), Z_1−β_ is the critical value for a power of 80% (0.842), d is 0.5. Using these values and applying a Bonferroni correction for multiple comparisons (α′ = 0.017).

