### 2.12 Statistical analysis

The normality of continuous variables will be evaluated using the Shapiro-Wilk test. Variables following a normal distribution will be reported as mean (standard deviation), while non-normally distributed variables will be expressed as median (interquartile range). The continuous data of normal distribution were analyzed by 1-way analysis of variance, and the continuous data of nonnormal distribution among the three groups were analyzed by the Kruskal-Wallis rank-sum test. Categorical data were analyzed using the χ^2^ test or Fisher’s exact test, and the P value was adjusted according to Bonferroni method and fixed at 0.017 for pairwise comparison. P < 0.05 was considered to indicate significance.

Outcome analyses for the primary endpoint will primarily follow a modified intention-to-treat (mITT) approach, including all participants for whom relevant data are available, regardless of protocol adherence. Additionally, a per-protocol (PP) analysis will be conducted, excluding participants with protocol deviations or those who withdrew consent, to evaluate the treatment effect among those who strictly followed the study protocol. The primary outcome is the ARCI-MBG score measured 30 min post-awakening. To account for potential confounders, a covariate-adjusted linear mixed model (LMM) will be utilized. The model will incorporate fixed effects for group (treatment group), time points (30 min post-awakening, 1 week, and 1 month), and the interaction between group and time to evaluate differences across groups over time. Potential confounders, including HADS scores, sex, age, BMI, comorbidities, smoking status, alcohol consumption, education level, and the number of painless examinations, will be included as covariates in the model. Sensitivity analyses will be conducted using both mITT and PP approaches to evaluate the robustness of the findings. Additionally, these analyses will adjust for potential confounders such as sex, age, BMI, comorbidities, smoking status, and education level, to further assess the consistency of the results across different analytical methods. No interim analysis will be planned. Missing data will not be imputed. Statistical analyses will be conducted with the use of SPSS software (V.25.0; IBM SPSS).

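### The no-imputation rule is justified only for procedure-day data, and with nine model covariates it could exclude patients whose primary outcome was observed

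*Protocol article*

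**What the plan says.** Section 2.12 states without qualification: "Missing data will not be imputed". The same section sets the main analysis population as modified intention-to-treat, "including all participants for whom relevant data are available, regardless of protocol adherence". It analyses the primary outcome with a linear mixed model that has group, time (30 minutes, 1 week, 1 month) and their interaction. Nine baseline covariates enter: HADS, sex, age, BMI, comorbidities, smoking, alcohol, education and number of painless examinations. Continuous variables in general go to one-way ANOVA or Kruskal-Wallis.

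The Discussion gives two reasons for not imputing. One is that "since most of our data were collected in a hospital setting, the missing data represent only a very small fraction of the overall dataset". The other is that "the missing data are unlikely to be systematically related to key variables".

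On timing, the primary outcome is "assessed via in-person interviews at 30 min post-awakening" (section 2.4). Section 2.5 adds follow-up scores: "Secondary outcomes will include ARCI-MBG scores at 1 week and 1 month postoperatively", the same times for ARCI total, PCAG and LSD, and "Pittsburgh Sleep Quality Index scores at 1 week and 1 month postoperatively". The sample size in section 2.11 was set "Considering a 10% dropout rate".

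**The concern.** There are two linked problems.

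- **The rationale does not reach the data most at risk.** Collection in hospital says nothing about who answers a questionnaire a week or a month later. Declining to impute is not free of assumptions either. An ANOVA or Kruskal-Wallis test on those who responded assumes that, within arm, responders and non-responders do not differ in the outcome. If patients' experience on the procedure day influences who responds later, the follow-up comparisons of ARCI total, PCAG, LSD and PSQI could be biased.
- **The rule is wider than its rationale.** It covers all missing data, so it covers baseline covariates too. Standard mixed-model fitting omits records with a missing covariate. Because these covariates are fixed within patient, one blank field removes all of that patient's records, including an observed primary outcome. The trial would lose evaluable randomised patients for a reason that is easy to avoid.

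**Working it through.** **1. Where the efficacy assessments fall** (section 2.5 and Table 1)

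| Measure | Procedure day | 1 week and 1 month |
|---|---|---|
| MBG | 1 | 2 |
| ARCI total | 1 | 2 |
| PCAG | 1 | 2 |
| LSD | 1 | 2 |
| PSQI | 0 | 2 |
| Dream description | 1 | 0 |
| Surgical Pleth Index | 1 | 0 |
| Sum | 6 | 10 |

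So 10/16 = 62.5% of efficacy assessments, and two of the three time points in the mixed model, come after the procedure day.

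**2. Where all data fall.** Adding the nine baseline covariates and the nine safety outcomes of section 2.6 gives (6 + 9 + 9)/(16 + 9 + 9) = 24/34 = 71% collected on site. Adding six further items in Table 1 (three times, two satisfaction items, airway spasm) gives 30/40 = 75%. The statement that most data come from the hospital is therefore true of the whole dataset, but not of the efficacy outcomes.

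**3. The protocol's own sample size.** With the formula in section 2.11, n = (2.396 + 0.842)² × 2/0.5² = 83.9, so 84 per group. Then 84/0.9 = 93.3, so 94 per group, against the stated 95. A t-test calculation at α = 0.017 gives 85, and 85/0.9 = 94.4, so 95 exactly. The sample size is reproduced and is not in question here.

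**4. Loss from blank covariates.** The protocol gives no missing rate, so the rate m per field is an assumption. If k fields are each independently blank with probability m, the share of patients lost is 1 − (1 − m)^k. I use k = 9 for all covariates. I also use k = 6, leaving out age and BMI, which are eligibility criteria, and sex, which would hardly be blank. Power is for a two-group comparison with d = 0.5 and two-sided α = 0.017 (normal approximation), starting from 95 per arm with no other loss.

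| m | Lost, k = 6 | Of 285 | Power | Lost, k = 9 | Of 285 | Power |
|---|---|---|---|---|---|---|
| 0.25% | 1.5% | 4 | 0.849 | 2.2% | 6 | 0.846 |
| 0.5% | 3.0% | 8 | 0.843 | 4.4% | 13 | 0.837 |
| 1% | 5.9% | 17 | 0.831 | 8.6% | 25 | 0.818 |
| 2% | 11.4% | 33 | 0.804 | 16.6% | 47 | 0.776 |

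With no loss at all, power is 0.855. It stays at about 80% until 11 of 95 patients per arm are lost (95 − 84 = 11, or 11.6%). That needs m = 1 − (84/95)^(1/9) = 1.4% for nine fields, or 1 − (84/95)^(1/6) = 2.0% for six.

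**5. Which follow-up outcomes are exposed.** Section 2.12 ties the mixed model to the MBG score. A patient with only the 30-minute MBG stays in that model, and follow-up missingness that depends on the observed 30-minute score is missing at random, which a likelihood-based fit handles without imputation. If the other scores go to ANOVA or Kruskal-Wallis, then ARCI total, PCAG and LSD at two times each, plus PSQI at two, are compared in responders only: 3 × 2 + 2 = 8 of the 10 follow-up assessments.

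**The case against.** A reader might infer that the Discussion's premise is simply untrue. It is not. It speaks of most data and the overall dataset, and 71% to 75% of items are collected on site. It also suits the primary outcome, which is taken face to face on the day, and the covariates, which are taken at the pre-operative visit. Nor does the 10% dropout figure contradict it outright: a planning allowance for dropout is compatible with few missing items overall. What remains is that the premise does not reach the follow-up outcomes and that the two statements sit awkwardly together.

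A reader might also infer that the primary analysis will lose patients and power, perhaps to about 72%. That figure needs nine fields each blank in 2% of patients, independently, on top of the full 10% dropout (power 0.725 with 71 per arm). Dropout of that size is doubtful for a same-day outcome, blank fields tend to cluster within patients, and section 2.10 provides second-person verification of entries and regular audits. If the pre-operative fields are complete, nobody is lost. The power figures also ignore any precision gained from covariate adjustment. These points stand and push the likely loss towards the low end.

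Two further readings fail. The plan does not contradict its own modified intention-to-treat definition, because relevant data may be read to include model covariates; the wording is vague. And follow-up MBG is not open to bias merely because the 30-minute score predicts response, since the mixed model already covers that case.

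Finally, a rule for missing covariates is often left to an analysis plan. Here, though, the protocol itself fixes a blanket rule beside a nine-covariate model, so the stated rule is what needs changing.

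**Conclusion.** The concern holds in a limited form. The hospital-setting rationale supports the no-imputation rule for procedure-day data. It does not support assuming small, unrelated missingness for the 10 of 16 efficacy assessments at 1 week and 1 month. As worded, the rule would exclude a patient with an observed 30-minute MBG if any of nine covariates were blank.

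The size of that loss cannot be derived from the protocol. With six to nine fields independently blank in 0.25% to 2% of patients, it runs from about 1.5% to 17%, and the lower end is the more plausible. The risk of responder-only comparisons applies to follow-up ARCI total, PCAG, LSD and PSQI, on the reading that these go to ANOVA or Kruskal-Wallis. It does not apply to MBG under missing at random. That follow-up takes place away from the hospital is inferred from its timing; the protocol does not state the mode of contact.

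**What to change.** - **Section 2.12, rule:** limit the no-imputation statement to outcomes.
- **Section 2.12, covariates:** fill a missing baseline covariate with a single value computed blind to arm (mean or mode, or a missing category), so that every patient with an observed outcome stays in the model. Because the covariates precede randomisation and the filled value does not depend on arm, this does not bias the treatment contrast.
- **Section 2.12, other ARCI scores:** analyse total, PCAG and LSD with the same likelihood-based repeated-measures model as MBG, so that patients with only a 30-minute score contribute.
- **PSQI:** the same type of model can be used, but it can borrow only between 1 week and 1 month because there is no 30-minute value.
- **Discussion:** restrict the hospital-setting premise to procedure-day data, and do not present the missing fraction as already known.
- **Optional:** a delta-adjusted sensitivity analysis for 1-month MBG.

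The cost is wording in two places and a little programming, with no change to sample size or data collection. It should be settled before unblinding.
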